
### Study design

2.2.

Our study is a prospective, experimental, open, and non-randomized controlled trial.

This study research is carried out in the Child and Adolescent Psychiatry Department in Razi University Hospital-Manouba-Tunisia. It is conducted in collaboration with the C3RP team (Resource Center for Cognitive Remediation and Psychosocial Rehabilitation, Ile-de-France) -Sainte-Anne Hospital and under the supervision of [name] (Ph.D. – Professor of Psychology at Columbia University Irving Medical Center and Director of Cognitive Health Services for the New York State Office of Mental Health, United States).

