### Participants and screening

2.3.

The inclusion criteria are:

ο Adolescents aged than 13 years, meeting the Diagnostic and Statistical Manual for Mental Disorders (DSM-5) (4) criteria for ASD confirmed by the ADI-R [Autism Diagnostic Interview-Revised, (58)] criteria, without mental retardation, followed in the Child and Adolescent Psychiatry Department (out-patient clinic) in Razi University Hospital-Manouba-Tunisia. Patients who agreed to participate in our study were retained.ο Sufficient level of understanding and communication in Arabic and French (allowing them to understand the instructions during the care sessions).ο Regular school curriculum.

It should be noted that adolescents treated with psychotropics will be included, with the condition that there will be no change to the drug treatment (molecule, dosage) during the period of study.

A certified therapist will conduct a standardized interview for the clinical and diagnostic evaluation of these adolescents (using the ADI-R).

Parents obtained information concerning the study and had the opportunity to ask questions before agreeing to the participation of their children, and during the study.

The non-inclusion criteria are:

ο Out-of-school patientsο Mental retardation or severe cognitive impairmentsο A history of neurological disorderο Severe behavioral disordersο Electroconvulsive therapy in the past 6 months

Exclusion criteria are:

ο Non-achievement of the programο Missing more than three sessionsο Non-achievement of assessments after finishing the therapy

Strategies to improve adherence to intervention:

ο Method of choice: NEAR program enhances intrinsic and extrinsic motivation by employing more engaging and interesting exercises packages for cognitive practice, involving participants in choosing the focus of training.ο All candidates received two psycho-education sessions: one individual and one group session in order to raise their awareness, motivation and to present the program (number of sessions, progress, interest…).ο Parent involvement in the program and home tasks.

Our study will include 30 patients that will be divided into two groups: NEAR group/ control group (a group that will assign usual care).

This allocation of patients between the two groups would be made according to the following criteria:

ο Teenage motivationο Their availability and parent’s one to accompany them to their clinical evaluations and therapeutic sessions.

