The patients included in the NEAR group will be divided into three groups of five patients each. The rhythm for sessions for each group is one to two sessions per week. The duration of the program will be about 6 months.

In our study, the duration of the sessions will vary according to the capacities of the participants and the exchanges between them (about 90–120 min).

Two pre-trained therapists lead the sessions and are assigned to follow the progress of each participant.

All selected patients will have an assessment of global functioning, cognitive function (social cognition and neurocognition) pragmatic skills, social skills and self-esteem, and at baseline (T1), 1 week after the end of the NEAR program (T2), and 6 months later (T3). The same interval will be kept for three sessions of evaluations of the control group.

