#### Global functioning

2.4.1.

ο Global Assessment of Functioning (GAF):

In our study, the GAF is used to evaluate subjectively the social and psychological functioning of the participants and the impact of psychiatric illness on an individual’s life and daily functional skills and abilities. Scores range from 100 (“extremely high functioning”) to 1 (“severely impaired”). It differentiates 10 levels of psychosocial functioning (59). A higher score reflects higher functioning in everyday life based on scored criteria.

ο Behavior Rating Inventory of Executive Function (BRIEF):

Executive function behaviors in the school and home environments will be assessed using the BRIEF. This questionnaire is elaborated for parents and teachers of school-age children. It includes eight clinical scales (Behavioral regulation scales and Metacognition scales) and two validity scales (Inconsistency and Negativity) that give the clinician a well-rounded picture of the behavior of the adolescent being rated. The Global Executive Composite score takes into account all of the clinical scales and represents the adolescent’s overall executive function (60).

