#### Social skills

2.4.5.

The Social Responsiveness Scale (SRS) (77) is a validated questionnaire for assessing the ability to engage in emotionally appropriate reciprocal social interactions, communication, and stereotypies in autism. The scale is filled out by parents and measures the degree of social impairment in participants. Five subscales are distinguished: awareness of the relational environment, social cognition, social communication, social motivation, and mannerisms. It comprises 65 items on a 4-point Likert scale generating one total score (max. 195). A coefficient of social reciprocity is calculated by combining these different subscales. High scores are associated with more severe social impairments. The SRS scores correlate strongly with algorithm scores of the ADI-R (78).

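### Availability for the evaluations helps choose the arm, although both arms must attend them; with the post-allocation exclusions this risks differential, informative loss of outcomes whose size and direction the article cannot settle

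*Protocol article*

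**What the plan says.** Study design calls this a "prospective, experimental, open, and non-randomized controlled trial". Under Participants and screening, "Our study will include 30 patients that will be divided into two groups". The NEAR patients are "divided into three groups of five patients each", which makes 15 and leaves 30 − 15 = 15 for usual care.

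The same section fixes how the arm is chosen: "This allocation of patients between the two groups would be made according to the following criteria". Two criteria follow. One is the adolescent's motivation. The other is the availability of the adolescent, and of the parent "to accompany them to their clinical evaluations and therapeutic sessions".

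Every patient is assessed at baseline (T1), one week after the program (T2) and six months later (T3). For usual care, "The same interval will be kept for three sessions of evaluations of the control group". Only NEAR has sessions to attend, one or two a week for about 6 months.

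The section also lists exclusions that take effect after allocation: the program not completed, more than three sessions missed, and assessments not completed once therapy has ended.

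Statistical analysis describes one group-by-time test, a repeated-measures ANOVA comparing the arms at baseline and at completion of the intervention. The primary outcomes are the GAF and the BRIEF Global Executive Composite. On the BRIEF, Global functioning says "This questionnaire is elaborated for parents and teachers of school-age children". On the SRS, Social skills says "The scale is filled out by parents". The CCC-2 is rated by a parent or caregiver (Pragmatic skills).

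Trial status reports 26 recruited, 15 of them in NEAR.

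**The concern.** Availability for therapy sessions can matter only for NEAR. Availability for evaluations is needed equally in both arms and therefore belongs among the eligibility criteria. Once it helps pick the arm, the arm is tied to a factor that governs whether T2 and T3 are observed at all.

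This is separate from baseline confounding. Covariate adjustment for baseline scores, which the article foresees, cannot restore a T2 value that was never collected. Even if the arms matched perfectly at T1, the comparison would be distorted if the families who return differ in their change from those who do not, and if the proportion returning differs by arm.

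The exclusions add a second route to the same problem. Removing NEAR patients who do not finish, or who miss more than three sessions, is also selective, and it acts on the other arm. At stake is the T1-to-T2 contrast on the GAF and the BRIEF composite, with at most 15 patients per arm. T3 is outside that described test; loss there affects the maintenance follow-up, which serves the article's stated aim of sustaining skills.

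**Working it through.** **Plan's own figures.** The article gives no attendance rate, dropout rate, effect size or power, so there is nothing to reproduce beyond 3 × 5 = 15 NEAR and 30 − 15 = 15 control. All completion rates and correlations below are assumptions.

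**1. Shift from selective return.** Let a fraction p of an arm return, and let r be the correlation between willingness to return and change. Under a normal model, the mean change among returners exceeds that of the whole arm by r × φ(z_p)/p SD, where z_p is the standard normal quantile of p. The contrast shifts by the difference of this term between arms.
- p = 0.70: φ(0.524)/0.70 = 0.348/0.70 = 0.497.
- p = 0.90: φ(1.282)/0.90 = 0.175/0.90 = 0.195.
- Difference: 0.497 − 0.195 = 0.302.

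| Completion NEAR v control | r = 0 | r = 0.3 | r = 0.5 |
|---|---|---|---|
| equal | 0 | 0 | 0 |
| 90% v 70% | 0 | 0.09 SD | 0.15 SD |
| 95% v 60% | 0 | 0.16 SD | 0.27 SD |
| 70% v 90% | 0 | −0.09 SD | −0.15 SD |

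Positive entries mean that the control change is overstated relative to NEAR (for r > 0, with change counted as improvement), which works against NEAR. Negative entries favour NEAR.

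**2. Cross-check by a simpler route.** The shift in a completers-only mean is the missing fraction times the gap between completers and non-completers. With 30% missing in control and a gap of 0.25 to 0.8 SD, it is 0.30 × 0.25 = 0.075 to 0.30 × 0.8 = 0.24 SD. The same gap with 10% missing in NEAR takes back 0.025 to 0.08 SD, leaving a net 0.05 to 0.16 SD. The order of size agrees with step 1.

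**3. Precision.** The standard error relative to 15 v 15 is √(1/n₁ + 1/n₂) ÷ √(2/15).
- 90% v 70% (13.5 v 10.5): √0.1693 ÷ √0.1333 = 1.127.
- The same 24 patients split 12 v 12: √(15/12) = 1.118.
- 95% v 60% (14.25 v 9): 1.166; the same total split evenly (11.625 each): √(15/11.625) = 1.136.

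In the first case about 12 of the 13 percentage points come from losing six patients in total, and only about one from the imbalance. In whole patients (14 v 10), the difference detectable with 80% power (two-sided 5%, normal approximation) rises from 1.02 to 1.16 SD, and power for 1 SD falls from 78% to 68%. The reverse pattern, 10 v 14, gives the same figures.

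**4. Direction.** The binomial chance that controls have strictly more missing than NEAR (15 per arm) is 88% if the missing rates are 10% NEAR and 30% control, 41% if both are 20%, and 20% if they are 30% NEAR and 20% control. The answer depends wholly on rates that the article does not give.

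**5. Who can still be affected.** 26 − 15 = 11 recruited outside NEAR, and 30 − 26 = 4 places left. NEAR is already at its planned 15, so these four are apparently all controls.

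**The case against.** A reader might infer that availability decides the arm, that missing T2 and T3 data will concentrate in controls, and that NEAR will be nearly complete. The article does not support this. Motivation is a joint criterion, and availability covers evaluations and therapy together. A family unable to come weekly for 6 months may well manage three evaluations, and controls are already followed in the same out-patient clinic. Nowhere does the text say that less available families go to usual care; that is a natural inference, since only NEAR has sessions. NEAR also carries the heavier attendance burden and the exclusions for missed sessions and an uncompleted program, so its loss could equal or exceed that of controls. All of this stands, and it is why no direction is claimed here.

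Nor does the interval widen mainly because loss falls on one arm: most of the increase is total loss. Missing T3 alone removes nobody from the group-by-time test as described.

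Two further objections are fair. Handling of missing data and the mode of questionnaire completion are details that an article may leave to fuller documents. The point therefore rests on the stated allocation rule and the stated exclusions, not on an absent section. And a mixed model assumes missing at random, whereas the mechanism feared here is return linked to unseen change. The model lessens that bias but does not cure it.

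None of this answers the central fact: a requirement common to both arms is written as a reason for assigning one of them.

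**Conclusion.** The point holds as a risk, not as a predicted bias. Using availability for evaluations to help choose the arm, together with exclusions that act after allocation and a test that in its usual form needs both baseline and T2, exposes the GAF and BRIEF comparison to differential and informative loss. Heavier loss in controls is plausible; offset or reversal by the NEAR-only exclusions is possible too.

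The illustrative size is 0 to 0.15 SD at 90% v 70% completion, zero at equal completion, and of opposite sign if the rates are swapped. The standard error rises about 13%, nearly all of it from fewer patients overall. These figures rest on assumed completion rates, an assumed correlation of 0 to 0.5, 15 patients per arm, the repeated-measures ANOVA being run on complete cases, and the exclusions applying to the analysis as listed. With 26 of 30 recruited, the allocation rule itself can be repaired for about four patients only; what happens to the analysis set matters more.

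**What to change.** 1. For patients still to be recruited, make availability for all three evaluations an entry condition and delete it from the allocation criteria. Only availability for therapy sessions could then bear on the arm.
2. Keep every allocated patient in the analysis instead of excluding those with missed sessions, an unfinished program or missing assessments. Analyse the GAF and the BRIEF composite with a mixed model using all observed T1, T2 and T3 data in place of a complete-case repeated-measures ANOVA. The model helps only if the exclusions no longer remove patients from the analysis.
3. For evaluations still ahead, allow the BRIEF, SRS and CCC-2 to be returned without a clinic visit, in the same mode in both arms. The GAF would still need contact with an assessor.
4. Report T2 and T3 completion by arm.

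The cost is a few lines in the allocation, exclusion and analysis text, postal or electronic return of questionnaires already in use, and a different SPSS procedure. There are three downsides: questionnaires are completed unsupervised; controls entered under the new condition may differ slightly from those already recruited; and the missing-at-random assumption means that selection bias is reduced rather than removed.

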## Statistical analysis

3.

Data collection and statistical analysis will be performed using the Statistical Package for Social Sciences (SPSS) version 25.

We will proceed to the comparison of the different scores of each group at the beginning and at the end of the study as well as to the comparison of the progression of the two groups between them at the beginning and at the end of the study.

The primary objective of our study is to facilitate the transfer of new skills to daily life and thus the global functioning of this population. Primary outcomes will be based on the GAF score and The Global Executive Composite score of the BRIEF. All other measures (social cognition, neurocognition, social skills, pragmatic skills and self-esteem) will be secondary outcomes and will be assessed descriptively.

For the descriptive statistics, we will calculate means and standard deviations for age and educational level and for categorical data, e.g., sex we will use Fisher’s Exact Chi-squared test.

For each neurocognitive and social cognition domain measure, we will conduct *t*-tests for independent samples to examine baseline differences for this sample. To examine Group X Time interaction for measuring treatment effects, we will conduct a Repeated Measure-Analysis of Variance (RM-ANOVA) that compared the difference scores of NEAR-group vs. Control-group at baseline and at the completion of the intervention.

A RM-ANOVA will also be used to examine differences in pragmatic skills, social skills and self-esteem.

For the two measures where there were statistically significant baseline differences, we will repeat the RM-ANOVA using baseline cognitive scores as a co-variate to control for baseline differences.

The significance level for all statistical analyses will be set to *p* = <0.05.

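### The RM-ANOVA has no term for the three NEAR therapy groups, so the standard error of the NEAR–control difference is too small if outcomes within a group are positively correlated

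*Protocol article*

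**What the plan says.** Section 2.3 (Participants and screening) sets the size: "Our study will include 30 patients that will be divided into two groups". On delivery it says: "The patients included in the NEAR group will be divided into three groups of five patients each". The comparator is a "control group (a group that will assign usual care"; no therapy groups are described for it. Each NEAR group meets once or twice a week, and "the duration of the sessions will vary according to the capacities of the participants and the exchanges between them". On staffing: "Two pre-trained therapists lead the sessions and are assigned to follow the progress of each participant".

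Section 3 (Statistical analysis) gives the test: "To examine Group X Time interaction for measuring treatment effects, we will conduct a Repeated Measure-Analysis of Variance (RM-ANOVA", comparing the arms at baseline and at completion. The one adjustment it plans is a baseline score as covariate for measures that differ at baseline. The significance level is 0.05 throughout. Therapy group, clustering and intraclass correlation are not mentioned anywhere in the article.

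**The concern.** This is a partially nested design: NEAR patients are clustered in therapy groups and controls are not. Five adolescents who share a bridging group also share peers, group dynamics and the rhythm of their sessions, so their changes may resemble one another more than those of adolescents in different groups. An RM-ANOVA with the patient as the only unit assumes that this does not happen.

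If the correlation is positive, the mean of the NEAR arm varies more than the model believes. The reported standard error of the NEAR–control difference is then too small and the p-value too optimistic. At stake is whether a nominally significant difference in GAF or GEC would stay significant once the grouping is allowed for.

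**Working it through.** **The plan's own figure.** The article gives 30 patients without a power calculation, effect size, standard deviation or ICC, so there is no derivation to reproduce. The arithmetic is consistent: 3 × 5 = 15 NEAR patients, which leaves 30 − 15 = 15 controls.

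**Inputs.** From section 2.3: m = 5 per group, 3 groups, 15 NEAR patients, and 15 controls by subtraction. From section 3: level 0.05, taken as two-sided because the article does not say. Assumed: ICC of 0.01, 0.05, 0.10 or 0.20 for the change score, and equal total variance (set to 1) in both arms. With two time points, the Group × Time F-test is equivalent to a two-sample t-test on change scores, so the check uses that test.

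**Step 1: true variance of the difference.** The design effect applies to the NEAR arm only: DE = 1 + (m − 1) × ICC = 1 + 4 × ICC. The true variance is DE/15 + 1/15 = (2 + 4 × ICC)/15.

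**Step 2: variance that the test reports.** Positive correlation also pulls the sample variance in the NEAR arm down. Its expectation is (15 − DE)/14 = 1 − 4 × ICC/14. The expected reported variance is therefore (2 − 4 × ICC/14)/15.

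**Step 3: ratio.** True SE / reported SE = √[(2 + 4 × ICC)/(2 − 4 × ICC/14)]. At ICC 0.20 this is √(2.8/1.943) = 1.20.

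**Step 4: type I error.** Simulation of three clusters of five against 15 single controls, 200,000 runs per ICC, ordinary t-test:

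| Assumed ICC | DE (NEAR arm) | Effective NEAR n = 15/DE | True SE / reported SE | Type I error at nominal 5% |
|---|---|---|---|---|
| 0.01 | 1.04 | 14.4 | 1.01 | 5.2% |
| 0.05 | 1.20 | 12.5 | 1.05 | 6.2% |
| 0.10 | 1.40 | 10.7 | 1.10 | 7.4% |
| 0.20 | 1.80 | 8.3 | 1.20 | 10.0% |

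At ICC 0 the ratio is 1.00 and the error rate is about 5%.

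**Step 5: does a fixed-ICC correction work?** Multiplying the reported standard error by the ratio for the correct ICC, with 28 degrees of freedom, brings the simulated type I error back to between 4.9% and 5.2% across the four values.

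**Step 6: cost of estimating the clustering instead.** A test of the three NEAR group means against the 15 controls, with Satterthwaite degrees of freedom, was simulated for a standardised difference of 1.06. That is the difference the independence test detects with 80% power at ICC 0. Power of the cluster-based test is about 0.67, 0.63, 0.58 and 0.51 at the four ICCs, and only 0.68 even at ICC 0.

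**The case against.** The strongest objection is that everything depends on an ICC that the article does not give. At 0.01 the test is close to nominal, and the individual computer exercises described in section 2.1.1 would pull any correlation down. This stands, so the finding is conditional and the range must include small values. A reader might infer that the standard errors are certainly too small; the documents do not support that.

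Other stronger readings also go beyond the text:

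- **Half of every session is group discussion.** The equal split in section 2.1.1 describes the programme as run in France. Section 2.3 gives about 90–120 minutes for this study and no split.
- **Role-play, games and team building run throughout.** Section 2.1.2 lists them as tools for Module 6, the module on communication.
- **Session length differs by group.** Section 2.3 ties it to the participants and their exchanges and does not state a difference between groups.
- **Shared therapists make it worse.** Section 2.3 does not say outright that the same two lead all three groups. If they do, the therapist is constant across groups and adds no between-group variance. The therapist effect would instead be confounded with the NEAR arm, which is a different problem.
- **Every outcome is affected, with confidence intervals too narrow.** Section 3 ties the RM-ANOVA to cognition, pragmatic skills, social skills and self-esteem. It also calls the secondary measures descriptive and promises no confidence intervals. For GAF and GEC the RM-ANOVA is implied only, though no other between-group test is offered.

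It can also be said that random effects belong in an analysis plan that is not shown. That carries less weight here. Section 3 names the test, its interaction term and its one covariate adjustment, so this is a stated analysis that does not fit the stated delivery, rather than a detail left open.

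Finally, allocation by motivation and availability (section 2.3) threatens any p-value more than clustering does. That is correct, and a clustering correction does not repair it. Equally, that bias does not make an understated standard error acceptable.

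**Conclusion.** The point holds in conditional form. Followed as written, section 3 understates the standard error of the NEAR–control difference whenever the within-group correlation is above zero. A positive value is plausible because the bridging groups are shared and session rhythm is set by group.

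The effect is negligible at an ICC of 0.01, modest at 0.05 to 0.10, and a doubling of the false-positive rate at 0.20. These figures rest on the assumed ICCs, 15 patients analysed per arm, equal variances and a two-sided 5% test. They also treat the arms as otherwise exchangeable, which the allocation method does not secure. The exclusion rules for non-completion and for missing more than three sessions may make the analysed groups smaller and unequal, which would change the factors somewhat.

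**What to change.** In section 3, state that therapy-group membership will be recorded and that the GAF and GEC group differences will be reported twice: as planned, and with the standard error inflated for clustering in the NEAR arm at fixed ICCs of 0.01, 0.05, 0.10 and 0.20. With 15 patients per arm the multipliers are 1.01, 1.05, 1.10 and 1.20; recalculate them from the group sizes actually analysed. Say for each outcome whether the conclusion survives across the range. Name the RM-ANOVA explicitly as the test for GAF and GEC if that is what is meant.

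A partially nested mixed model, with a random therapy-group effect in the NEAR arm only and small-sample degrees of freedom, may be added as supportive. It should not be the main remedy, because three clusters estimate the between-group variance poorly.

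The change costs a few sentences and needs no new measurements beyond a record of who sat in which group. The price is wider intervals, larger p-values and lower power.
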